### Data management

All case report forms (CRFs) will be stored in a locked cabinet. The consent forms will be stored separately from the CRFs. Data from CRFs will be entered and locked by 2 data managers, and only authorized researchers will have access.

### Statistical analysis of the trial outcomes

Outcome data will be analyzed according to the intention-to-treat principle, including all randomly assigned participants after baseline assessment regardless of whether they receive the intervention. Missing data will be replaced by the data from the latest assessment. The outcome data will be analyzed with SPSS (version 22.0; SPSS Inc., Chicago, IL, USA). Descriptive statistics (variance analysis, non-parametric test, chi-square test) will be used to summarize demographic features among the three groups. The HAMD-17, BPI, MoCA, and WHOQOL-BREF will be analyzed using the repeated measures method, and post hoc comparisons will be evaluated with the Bonferroni test. The rates of depression/pain response and depression remission will be analyzed by the chi-square test. P300 and blood measures will be analyzed by paired *T* tests.

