**Methods:**

This is a randomized, sham acupuncture-controlled trial with three arms: real acupuncture (RA), sham acupuncture (SA), and healthy control (HC). Forty-eight depression combined CMSP participants and 12 healthy people will be recruited from GDTCM hospital and randomized 2:2:1 to the RA, SA, and HC groups. The patients will receive RA or SA intervention for 8 weeks, and HC will not receive any intervention. Upon completion of the intervention, there will be a 4-week follow-up. The primary outcome measures will be the severity of depression and pain, which will be assessed by the Hamilton Depression Rating Scale (HAMD-17) and Brief Pain Inventory (BPI), respectively. The secondary outcome measures will be cognitive function and quality of life, which will be measured by the Montreal Cognitive Assessment (MoCA), P300, and World Health Organization Quality of Life (WHOQOL-BREF). In addition, the correlation between brain-derived neurotrophic factor (BDNF) and symptoms will also be determined.

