## Methods

### Study design

This project is a randomized controlled clinical trial with 3 groups: real acupuncture (RA), sham acupuncture (SA), and healthy control (HC) at a ratio of 2:2:1. This trial was approved by the ethics committee of Guangdong Provincial Hospital of Chinese Medicine (Z2017-162-01). Before randomization, written informed consent will be obtained from all participants prior to their involvement. Primary and secondary outcome measures will be assessed at baseline, 4, 8, and 12 weeks. Outcome assessors and statisticians will be blinded in this study. An overview of the trial is shown in Fig. 1. This protocol was reported according to the Standard Protocol Items: Recommendation for Interventional Trials (SPIRIT) statement requirements. The complete SPIRIT checklist is available in Additional file 1 and Fig. 2.

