### Real acupuncture treatment

Participants in the RA group will receive acupuncture at Baihui (DU20), Yintang (EX-HN3), Renzhong (DU27), Chenjiang (RN24), Hegu (LI4, bilateral), and Taichong (LR3, bilateral). After skin disinfection, sterile adhesive pads will be placed on the above points, and then needles (Hwato, Suzhou, China) will be inserted through the pad. At the DU20 and EX-HN3 points, needles will be obliquely inserted about 16 mm deep, and at the DU27, RN24, L14, and LR3 points, needles will be vertically inserted approximately 12 mm, 12 mm, 25 mm, and 25 mm deep, respectively. All these points will be stimulated manually until patients feel heaviness, soreness, distension, or numbness sensation (deqi), as reported in our previous study [15]. Each acupuncture session will be continued for 30 min and then the pads will be removed with a disinfection swab. The acupuncture treatment will be administered twice per week for a total of 16 sessions over a period of 8 weeks.

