### Discontinuations

If participants are unable or unwilling to complete the treatment, we consider will them to be treatment dropouts. This could occur if participants withdraw consent to receive the study intervention or if the psychiatrist assessment suggests that it is inappropriate to continue the study intervention due to, for instance, depression or pain condition persists or getting worse, serious suicidal ideation, or a severe adverse event.

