### Outcome measures

#### Primary outcomes

The primary outcomes are the changes in HAMD-17 and BPI scores from baseline to 12 weeks. HAMD-17 is a 17-item self-reported questionnaire; the higher the score is, the more severe the depression. A previous study showed that HAMD-17 has good validity and reliability for the assessment of depression severity. The BPI was first developed to measure pain in cancer patients, but it has become one of the most widely used pain measures, used for musculoskeletal pain and postsurgery pain [20, 21]. The BPI is a 15-item inventory that contains 2 dimensions: the intensity of the pain and interference with everyday activities. All the items are measured using a numerical rating scale from 0 to 10. The higher the score, the more severe the pain is.

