## Discussion

Depression and CMSP commonly coexist, which makes clinical treatment very difficult [29]. Despite huge costs, current pharmacological and psychological interventions have limited acceptability and effectiveness. Thus, patients are keen to have a cost-effective treatment. According to the American College of Physicians, acupuncture increases the response to second-generation antidepressants [30]. Previous studies also showed that acupuncture has clinical efficacy on depression and related symptoms, such as insomnia [15, 17, 18]. A systematic review showed that acupuncture is a cost-effective treatment for chronic pain [31]. Whether acupuncture has clinical efficacy on combined depression and CMSP is uncertain. On this basis, we designed this study, which meets CONSORT guidelines [32]. This trial will provide evidence on the clinical efficacy of acupuncture as a potential treatment for comorbid depression and CMSP. In addition, we will explore the mechanism of acupuncture’s antidepressant and analgesic effects from an epigenetic perspective.

Even so, there are some limitations of this study. First, it is a single-blind study, which may cause partial bias in the results. We will try our best to overcome this bias by allocating the different groups in different places to receive treatment. Second, the adherence of participants may be poor because the treatment period lasts 8 weeks. The study size is calculated on the hypothesis of a 15% loss rate, but it will be necessary to ascertain that there is no bias between the two intervention groups. Third, in this study, we performed a 4-week follow-up, and long-term follow-up will be more credible. Finally, there will be a skewed sex ratio in this study, because in traditional Chinese culture, men are generally unwilling to seek help, especially for mental disease. This bias was also present in our previous study.

We have presented the design and protocol for the clinical efficacy of acupuncture on mild-moderate depression comorbid with CMSP. On completion, this study will validate the clinical efficacy of acupuncture and its underlying mechanism.

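### Carrying the last observation forward to week 12, four weeks off treatment, can bias the primary real-versus-sham comparison in either direction

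*Protocol article*

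**What the plan says.** The section on statistical analysis of the trial outcomes gives one rule for every outcome: "Missing data will be replaced by the data from the latest assessment". It stands beside an intention-to-treat population, "including all randomly assigned participants after baseline assessment regardless of whether they receive the intervention", and an otherwise undescribed repeated-measures analysis of HAMD-17, BPI, MoCA and WHOQOL-BREF with Bonferroni post hoc comparisons.

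The time points are fixed elsewhere in the article:
- Primary outcomes section: "The primary outcomes are the changes in HAMD-17 and BPI scores from baseline to 12 weeks".
- Study design section: "Primary and secondary outcome measures will be assessed at baseline, 4, 8, and 12 weeks".
- Real acupuncture treatment section: sessions are given "twice per week for a total of 16 sessions over a period of 8 weeks".
- Abstract, Methods: "Upon completion of the intervention, there will be a 4-week follow-up".

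Week 12 is therefore an off-treatment visit. The values that can be carried into it are the baseline, week-4 and week-8 scores.

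On loss, the sample size section allows for 15% dropout at the end of treatment. The Discussion says that "the adherence of participants may be poor because the treatment period lasts 8 weeks", repeats the 15% figure, and adds that absence of bias between the two intervention groups will have to be confirmed.

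**The concern.** LOCF assumes that a participant's score stays where it was when last seen. Two features of this trial make that a poor assumption for the primary comparison.

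**Early loss.** If scores improve over time in both arms, someone last seen at baseline or week 4 is frozen at a higher (worse) score than they would probably have reached. The arm that loses more people early then looks worse, even if treatment does nothing.

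**Loss after week 8.** Someone who misses only week 12 contributes a score taken at the end of treatment to an endpoint meant to describe the state four weeks later. If an acupuncture benefit fades over those weeks, LOCF keeps it alive for these participants. This needs no imbalance in dropout.

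The RA–SA difference on HAMD-17 and BPI at week 12 is at stake. Analysing everyone as randomised keeps participants in the denominator, but it does not make the carried-forward scores right.

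The article states this rule outright, so the point does not turn on detail that an unseen analysis plan might add.

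**Working it through.** The plan has no figure of its own to reproduce here. The check asks how large the LOCF bias would be under stated assumptions.

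**From the article:** 24 patients per arm (sample size section); visits at 0, 4, 8 and 12 weeks; endpoint is change to week 12; treatment ends at week 8; planned loss 15%.

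**Assumed, because the article gives none:** HAMD-17 SD 5 at each visit; correlation 0.6 between visits; the mean courses and dropout patterns below; dropout unrelated to the score. No separate BPI calculation was made.

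**Formula.** Let p_k be the proportion of an arm last seen at visit k, and μ_k the mean at that visit. LOCF shifts the arm's expected week-12 mean by Σ p_k(μ_k − μ_12). The bias in the difference is the RA shift minus the SA shift. A negative value favours RA.

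**1. No true difference.** Both arms follow 18, 15, 12, 10. Those last seen at baseline, week 4 or week 8 are frozen 8, 5 or 2 points too high.
- Equal dropout in both arms: the shifts cancel and the bias is 0.
- RA 5/3/2% (10%), SA 12/5/3% (20%):
  - RA shift = 0.05×8 + 0.03×5 + 0.02×2 = 0.59
  - SA shift = 0.12×8 + 0.05×5 + 0.03×2 = 1.27
  - Bias = 0.59 − 1.27 = −0.68
- RA 3/1/1% (5%), SA 17/5/3% (25%):
  - RA shift = 0.24 + 0.05 + 0.02 = 0.31
  - SA shift = 1.36 + 0.25 + 0.06 = 1.67
  - Bias = −1.36

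**2. Benefit that fades.** RA 9 and SA 12 at week 8, both 13 at week 12, with 15% of each arm missing only week 12. Bias = 0.15×(9−13) − 0.15×(12−13) = −0.60 + 0.15 = −0.45.

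**3. Simulation.** 20,000 trials per scenario, two-sample t test on the LOCF week-12 change:

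| Scenario | Bias (points) | Type I error | Mean model SE | Empirical SD |
|---|---|---|---|---|
| Equal dropout, same course | 0.00 | 4.9% | 1.40 | 1.40 |
| 10% vs 20% | −0.66 | 7.5% | 1.41 | 1.41 |
| 5% vs 25% | −1.36 | 16.0% | 1.40 | 1.41 |
| 3-point week-8 benefit gone by week 12, 15% per arm missing week 12 | −0.44 | 6.2% | 1.32 | 1.32 |

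Simulation and formula agree to within 0.02 points.

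**4. Direction.** A separate set of runs used SD 4 and other courses.
- With no true difference, improvement then relapse in both arms, and 5% versus 25% dropout, the bias was +0.2, against RA.
- With a lasting 4-point benefit and equal dropout, LOCF shrank it to 3.7 points at 15% loss and 3.4 at 33%. The 33% is the loss that going from 32 to 48 patients would imply (1 − 32/48); the stated rate is 15%.

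**5. Does a likelihood approach do better?** In the SD 4 runs, a likelihood-type estimate assuming missing at random was compared with LOCF where the true week-12 difference was zero.
- Only sham non-responders tending to drop out (6% versus 31%): LOCF −1.5 points with 22% false positives; likelihood-type estimate 0.0.
- A 5-point week-8 benefit gone by week 12, 15% of each arm lost after week 8: LOCF −0.7 points with 10% false positives; likelihood-type estimate 0.0.

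**6. Precision.** In the table the model SE tracks the empirical SD, so the excess type I error comes from bias. In the SD 4 runs with a lasting effect, the LOCF SE was 1.06 against 1.12 from observed cases at 15% loss, and 1.09 against 1.26 at 33%. In a steadily improving null case at 15% loss it was slightly larger (1.16 against 1.12).

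**The case against.** **The sizes are assumed.** This stands. The article gives one overall loss rate and nothing by arm. At 13% versus 17% the bias is about 0.30 points with 5.7% type I error. The 16% figure needs five times as much dropout in sham, which blinded participants and a pad-based sham at the same points make less likely, though not impossible. In the fading scenario the bias is about a third of a standard error (0.44/1.32 = 0.33). The article also calls the study a pilot.

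**Stopping treatment is not the same as missing an assessment.** This also stands. A reader might infer from the Discontinuations section, whose examples include "depression or pain condition persists or getting worse, serious suicidal ideation, or a severe adverse event", that week-12 scores will be missing for outcome-related reasons. That section defines treatment dropouts and does not say that their assessments stop, and the analysis population keeps them in. It shows that outcome-related loss is plausible, not that it will occur.

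**The test differs.** The simulation uses a t test on week-12 change, whereas the plan names a repeated-measures method with post hoc comparisons. The error rates are therefore indicative only. The bias in the mean week-12 difference does not depend on the test.

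**The replacement has its own assumption.** A mixed model relies on missing at random and does not cure dropout driven by unobserved worsening. True, but it does not require scores to stand still after the last visit.

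None of this defends LOCF as the sole rule for an off-treatment endpoint.

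**Conclusion.** The point holds as a criticism of a stated primary-analysis rule. LOCF can bias the week-12 RA–SA difference through unequal early loss, or through fading of an effect after week 8 even with equal loss. Under the assumed values the HAMD-17 bias ranges from nil (equal dropout, same course) to 0.66 points at 10% versus 20%, an average of the planned 15%, and to 1.36 points at 5% versus 25%. The corresponding type I error is 4.9%, 7.5% and 16%. The direction cannot be known in advance.

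Two stronger readings are not supported. A reader might infer that LOCF makes the standard errors too small as a rule. Treating carried-forward values as observed is wrong in principle and can understate uncertainty at higher loss, but at the planned 15% the effect is small and not consistent in sign. A reader might also infer that this trial will produce a false-positive result. The documents give no dropout by arm and no symptom course from which to say so.

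**What to change.** In the statistical analysis section, replace LOCF as the primary approach with a likelihood-based mixed model for repeated measures. Fit it to RA and SA using all observed week-4, week-8 and week-12 scores without imputation, and report the RA–SA contrast at week 12 for HAMD-17 and BPI. This is consistent with the repeated-measures method already named and is available in SPSS MIXED.

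State that participants who stop treatment are still assessed at the scheduled visits. LOCF may stay as a supportive analysis. Because the model assumes missing at random, a missing-not-at-random sensitivity analysis is desirable but optional.

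The cost is a change of wording and slightly more analysis work. The article reports that the study is still recruiting, so continued assessment can still be arranged. The analysis rule should be changed before unblinding, since a later change would look data-driven.

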## Background

Chronic musculoskeletal pain (CMSP) and depression are the leading causes of years lived with disabling disease worldwide [1]. Moreover, CMSP and depression are highly intertwined and could exacerbate one another’s symptoms [2, 3]. Unfortunately, the overlapping symptoms lead to poor physical functional outcomes, longer duration of symptoms, and lower treatment response. This places a profound burden on both individuals and society. Notably, this burden far exceeds social service capacity.

The high prevalence of depression and CMSP comorbidity may indicate a common pathogenesis. Both depression and chronic pain are associated with cognitive function [4]. An increasing number of studies have shown that people who suffer from chronic pain or depression have poor performance on cognitive function tests [5, 6]. Other studies found that cognitive function acts as a protective factor against the emergence of chronic pain. Brain-derived neurotrophic factor (BDNF) is a member of the neurotrophin family, which is crucial for the survival and neuroplasticity of neurons. Decreased BDNF levels and increased BDNF methylation status, especially in the promoter regions of exons I and IV, were identified in patients with depression [7, 8]. More interestingly, after antidepressive treatment, BDNF methylation decreased, and serum BDNF levels increased [9, 10]. Some studies have demonstrated that serum BDNF levels are tightly correlated with the course of depression [11]. Thus, some scientists consider BDNF and BDNF promoter methylation to be biomarkers for depression [10, 12–14].

Acupuncture has been widely used to improve chronic pain and depression [15–17]. However, research on depression comorbid with chronic pain is rare. A randomized, controlled trial of acupuncture or counseling compared with usual care for depression showed that acupuncture is a cost-effective treatment for depression patients with or without comorbid pain [18]. However, the evidence on the effect of acupuncture is not conclusive. Therefore, we propose to conduct a pilot RCT of acupuncture on comorbid mild-moderate depression and CMSP. The objective of this study is to (1) determine the clinical efficacy of acupuncture on comorbid mild-moderate depression and CMSP and (2) investigate the association between BDNF and comorbidity of depression and CMSP.

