### Intervention

The study intervention protocol was determined according to the classical principles of traditional Chinese medicine. All acupuncturists had at least 5 years of acupuncture experience. The participants will be asked not to take any other medications for pain or depression and, if they did, to document the pills and dosage. In addition, the HC participants will not receive any medical intervention, except blood and P300 tests at baseline.

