#### Secondary outcomes

Secondary outcomes include the rates of depression response and remission at the 8th week (endpoint), where response is defined as a reduction of 50% of the HAMD-17 score and remission as a HAMD-17 score of 7 or less [22]; the rates of pain response at the 8th week, where response is defined as a reduction of 2 points of the BPI-WP [23, 24]; the Beijing version of Montreal Cognitive Assessment (MoCA); the World Health Organization Quality of Life BREF (WHOQOL-BREF); event-related potential (P300); and the serum level of BDNF and DNA methylation of BDNF. The Beijing version of the MoCA is highly recommended as a clinical and research tool for evaluating cognitive impairment. Previous studies proved that B-MoCA has a reliability of 0.73 Cronbach’s alpha in patients with obstructive sleep apnea-hypopnea syndrome with cognitive impairment [25]. The total MoCA score is 30 points, and less than 26 points is considered to indicate cognitive impairment. In addition, P300 will be used as an objective index to measure cognitive impairment, because it is based on the electrophysiological brain response. Previous studies have shown a decrease in amplitude and an increase in latency in depression patients [26]. The WHOQOL-BREF is an abbreviated version of the WHOQOL-100, which contains 26 items. In this trial, the official Chinese version of the WHOQOL-BREF, which has been approved by the WHOQOL Group [27], will be used to evaluate the changes in quality of life. BDNF is a biomarker for depression patients [14, 28]. All depression and CMSP participants will receive blood tests and P300 tests at baseline and 8 weeks. ELISA, RT-PCR, and BSP will be applied to measure the serum BDNA level and BDNF DNA methylation. The correlation between BDNF and symptoms will be determined.

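### Serum BDNF, BDNF methylation and P300 get only a before-after paired t test, so no planned analysis compares real with sham acupuncture on the mechanism outcomes

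*Protocol article*

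**What the plan says.** All places are in the protocol article.

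- **Statistical analysis of the trial outcomes** gives each outcome a test. For the scales, "The HAMD-17, BPI, MoCA, and WHOQOL-BREF will be analyzed using the repeated measures method", with Bonferroni post hoc comparisons. Response and remission rates get a chi-square test. For the rest, "P300 and blood measures will be analyzed by paired" t tests.
- **Secondary outcomes** lists "the serum level of BDNF and DNA methylation of BDNF" alongside P300. On timing it says "All depression and CMSP participants will receive blood tests and P300 tests at baseline and 8 weeks". The only other BDNF analysis is a correlation with symptoms.
- **Intervention** says "the HC participants will not receive any medical intervention, except blood and P300 tests at baseline". On medication, patients are "asked not to take any other medications for pain or depression and, if they did, to document the pills and dosage".
- **Background** reports that "after antidepressive treatment, BDNF methylation decreased, and serum BDNF levels increased".
- **Abstract (Discussion)** gives the underlying mechanism of acupuncture as part of the aim, and the main **Discussion** closes by saying "this study will validate the clinical efficacy of acupuncture and its underlying mechanism".

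**The concern.** A paired t test asks whether patients differ from their own baseline. It does not ask whether real acupuncture changed them more than sham did. Between baseline and week 8, an acupuncture effect is mixed with the natural course of illness, regression to the mean, placebo response and changes in medication. The sham arm is in the design to separate these, and for BDNF, methylation and P300 the named test does not use it.

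Medication is a concrete example because the article supplies the link itself: the Background ties antidepressive treatment to higher serum BDNF and lower methylation, while drug use during the trial is only discouraged and recorded. The effect can run either way. Starting a drug would imitate a benefit on BDNF; stopping one at entry would tend to lower BDNF and hide a benefit.

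At stake is the mechanism claim. Running the paired test in each arm and noting that RA reached significance while SA did not would not rescue it, because that is not a test of the difference between arms.

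**Working it through.** **1. Can the named test be an arm comparison?** No. Under Randomization, patients are allocated to RA or SA by simple randomisation, and no matching is described. RA and SA patients are therefore independent, and the only pairs are a patient's own two measurements.

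**2. Is there another control?** Healthy controls are tested at baseline only. They have no second value to pair and cannot show change over time. SA is the only concurrent control for weeks 0 to 8.

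**3. Does another stated analysis fill the gap?** The repeated-measures list names four scales and omits P300 and blood measures. The BDNF-symptom correlation is not an arm contrast.

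The defect rests on these three steps alone. The plan states no figure to reproduce. The rest illustrates its size.

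**Inputs.** From Sample size calculation: 24 patients per arm, α = 0.05 (taken as two-sided), 15% dropout, so 24 × 0.85 = 20.4, about 20 per arm. Assumed, because the documents are silent: normal values with SD 1 at both times, baseline-to-week-8 correlation *r*, a shift *d* common to both arms, and no acupuncture effect.

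**4. How often is the RA paired test significant?** The SD of a change is √(2(1−r)), so the noncentrality is d√n / √(2(1−r)) on n−1 degrees of freedom. If the arms are independent and each is significant with probability p, then RA significant with SA not has probability p(1−p). At r = 0.5:

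| Common shift d (SD) | RA significant, n = 24 | RA significant, n = 20 | RA significant and SA not, n = 24 |
|---|---|---|---|
| 0.1 | 0.076 | 0.071 | 0.070 |
| 0.2 | 0.156 | 0.136 | 0.131 |
| 0.3 | 0.291 | 0.247 | 0.206 |
| 0.4 | 0.467 | 0.397 | 0.249 |
| 0.5 | 0.650 | 0.565 | 0.227 |

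At d = 0.3 and n = 24, the RA test is significant with probability 0.222 for r = 0.3 and 0.444 for r = 0.7. With no shift, the last column would be 0.05 × 0.95 = 0.048.

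**5. What does an RA-SA ANCOVA do in the same setting?** In 20,000 simulated trials per setting, with d = 0, 0.2 and 0.5, it rejected in 0.051, 0.048 and 0.050 (n = 24) and 0.049, 0.051 and 0.051 (n = 20). The common shift cancels.

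**6. Medication change alone** (n = 24, r = 0.5, 100,000 simulated trials per row). A net share of patients shifts by the amount shown:

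| Net share | Shift (SD) | Significant rise | Significant fall |
|---|---|---|---|
| 20% start | +0.5 | 0.066 | 0.008 |
| 20% start | +0.8 | 0.105 | 0.004 |
| 40% start | +0.5 | 0.146 | 0.002 |
| 40% start | +0.8 | 0.288 | 0.0004 |
| 20% stop | −0.5 | 0.008 | 0.068 |
| 40% stop | −0.8 | 0.0004 | 0.287 |

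At a net 10% the two-sided total is only 0.057 (0.5 SD) to 0.063 (0.8 SD), so small drug changes matter little.

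**7. Power cost of the arm comparison.** For 80% power, the paired test needs a noncentrality based on √(2(1−r)/n). ANCOVA uses √(2(1−r²)/n), widened by a factor √(1 + 1/(2n−4)) for chance baseline imbalance, on 2n−3 degrees of freedom.

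| n per arm | r | ANCOVA (SD) | Paired (SD) |
|---|---|---|---|
| 24 | 0.3 | 0.80 | 0.71 |
| 24 | 0.5 | 0.72 | 0.60 |
| 24 | 0.7 | 0.60 | 0.46 |
| 20 | 0.5 | 0.80 | 0.66 |

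**The case against.** Four points can be made for the plan.

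*The article is condensed.* It does not say that paired tests are the only analysis, and a fuller document could add an arm comparison. That would be a good answer had the method been left open. Instead the article names a method, and a different one from the other continuous outcomes. An analysis plan that follows it inherits the problem. What stands is a limit on wording: the only test named is within-arm; the article does not rule out another.

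*The rejection rates are not test errors.* If a shared shift exists, the paired null is false and rejecting it is correct. This stands. The percentages show how often a real change with another cause would be available to be credited to acupuncture; the error lies in the attribution. Nor does the article say that significance will be compared across arms.

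*The stakes are modest.* The Background calls the study a pilot, its BDNF objective is an association with the comorbidity, and the paired test is not what answers that. BDNF and P300 are secondary outcomes. This limits the weight, but the Abstract and Discussion still make a mechanism claim that needs the randomised contrast.

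*The medication material is not essential.* This largely stands. The documents give no rates of drug use, and randomisation protects the RA-SA contrast without a medication covariate. Medication is one illustration of a non-acupuncture cause, and the covariate is optional.

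**Conclusion.** The point holds, and the plan should be changed. The named test for serum BDNF, BDNF methylation and P300 bypasses the sham control, so a change by week 8 cannot support a claim about how acupuncture works. That conclusion needs no numerical assumption.

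The illustrated size depends wholly on assumed inputs. With no acupuncture effect and a shared 0.1 to 0.5 SD shift at r = 0.5, a significant RA change appears in 8% to 65% of trials with 24 per arm, or 7% to 57% with 20.

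The importance is minor to moderate: these are secondary outcomes. Nothing here implies that the RA-SA comparison on HAMD-17 or BPI is confounded, and nothing is claimed about the size or direction of bias in the BDNF-symptom correlation.

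**What to change.** Replace the sentence on P300 and blood measures with:

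> Week-8 serum BDNF, BDNF methylation and P300 will each be compared between RA and SA by ANCOVA with the baseline value as covariate and, if recorded, baseline antidepressant use (yes/no). Medication taken after randomisation will not be adjusted for. Within-arm paired changes will be reported as descriptive.

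The essential part is the RA-SA comparison adjusted for baseline. Post-randomisation medication is left out of the model because treatment may influence it. Optionally, repeat the BDNF-symptom correlation adjusted for baseline antidepressant use, labelled as a sensitivity analysis. The healthy controls' baseline values are a separate question that this sentence does not address.

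**Cost.** One sentence, using samples and P300 recordings already planned. The optional covariate needs at most one yes/no field on the case report form and one degree of freedom (with 24 per arm, critical t moves from 2.014 to 2.015). The real cost is power: at r = 0.5 the smallest effect detectable with 80% power rises from 0.60 to 0.72 SD with 24 per arm, and from 0.66 to 0.80 SD with 20. The paired test's extra power serves a question that does not isolate acupuncture.
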